**Fig. 1 Fig1:**
[figure not shown]
The Verily Study Watch (an Investigational Device), along with syncing/charging cradle and Study Hub. The photographs are owned by Verily and have a copyright. Verily kindly granted written permission to use and adopt if for this publication

### Subject retention strategies

Throughout the study, a dedicated helpdesk proactively assists participants, addresses problems and questions, and solves/communicates issues related to the execution of the trial. In addition to the study helpdesk, assigning a personal trial assessor to each participant during the entire study period is an important retention strategy. Participants are kept informed about the study with newsletters and participant events. In addition, the study website will be used for regular recruitment updates, combined with an extensive information package on topics that are found to be relevant for people with PD. The topics will be selected by the participants themselves.

### Quality management

All study procedures are being performed at a single centre, the Radboud university medical center. The study assessors were extensively trained and certified for the various elements of the protocol, before enrollment of the first study subject. Written standardized operating procedures (SOPs) were developed, detailing all data collection and study procedures. At least once a month, the study team discusses unexpected situations and problems encountered with execution of the study protocol. Frequent monitoring of the data quality ensures a timely identification of both systematic and incidental deviations. On a monthly basis an independent study monitor checks key elements of the study, e.g., inclusion rates, informed consents, data entry, protocol deviations, and (serious) adverse event reporting. If quality control issues emerge, the study protocol and SOPs will be amended and trial assessors will be retrained.

### Data management and protection to subject privacy

#### Data protection

For the PPP study, a Polymorphic Encryption and Pseudonymization (PEP) infrastructure was developed and is used to protect the data and the privacy of the participants [35]. For each participant, this method generates unique pseudonyms for the different participating research groups. The PEP was created to deal with the rigidity of the traditional encryption/decryption process by using polymorphic encryption right after collection and before storage. In that manner, there is no need to a priori fix in the encryption key for the data. The PEP system allows different researchers to have access to the entire dataset or only a subset of the dataset with a specific decryption key. In addition, the polymorphic encryption method avoids the combination of different datasets by different decryption key-holders, since each key only decrypts that subset of the data. Due to its additional security, the PEP is an ideal approach to manage sensitive personal data with reduced risk of a participant’s privacy being violated.

#### Data handling and storage

An electronic data capture and management system, Castor (https://data.castoredc.com), is used for the collection of most study data. This is a GCP-certified data management system with servers in accordance with the NEN7510 norm for information security in healthcare. All medical examinations and clinical assessment data are entered directly into Castor and stored in a pseudonymized manner. Similarly, Castor is used by subjects to complete the online questionnaires as part of the annual assessment. Holter ECG and 12-lead ECG data are also stored directly into Castor. MRI data is collected and stored at the Donders Center for Cognitive Neuroscience (DCCN), following their data management procedures: after data collection a backup is stored locally on the DCCN data servers; a copy is transferred to PEP, based on a PEP-generated pseudonym. Participating researchers can access data only via PEP. For the Verily Study Watch data, Verily will first preprocess the data and subsequently upload it to PEP. Verily only knows the device identifiers, but does not know the study participants.

All biospecimens are biobanked at the Radboud Biobank (Nijmegen, the Netherlands) [36], with their sample tracking system, sample processing system operation procedures, and standardized sample storage conditions being employed. In addition to Radboud’s laboratory capabilities, some sample processing will be performed by Verily Life Sciences. Verily has an on-site biobank as well as laboratories for molecular biology, chemistry, immunology, and systems biology including a population scale genomics facility. Verily’s laboratories use a laboratory information system for sample tracking, and all staff are trained on standard operation procedures for sample biobanking and processing. PEP pseudonyms for all samples have been added to both biobanks’ sample tracking systems.

### Statistical analyses

The primary objective of this study is to evaluate the rate of disease progression and, ultimately, to evaluate treatment response with respect to the presence of both established and potential biomarkers. More specifically, we will address two objectives in the short term:The individual associations between potential biomarkers and disease progression in Parkinson’s disease, with progression being expressed in terms of rate of decline in two key outcome domains of the disease, i.e., motor functioning and cognitive functioning.The prediction of disease progression after 1 year and 2 years on each of the two outcome domains.

Motor functioning will be determined using the score from the motor section (part III) of the Movement Disorders Society-sponsored revision of the Unified Parkinson’s Disease Rating Scale (MDS-UPDRS) [37], measured in the OFF state. Cognitive functioning will be determined using the score from the Montreal Cognitive Assessment scale (MoCA), a scale for global cognitive abilities that is validated for use in Parkinson’s disease [38].

For each of the two outcomes, the prediction will be made for absolute change scores (as a continuous measure) and clinically important change scores or clinically important threshold (as a dichotomous measure). For motor functioning, the dichotomous measure is a change of at least 5.5 [39, 40]. For cognitive functioning, the dichotomous measure is a follow-up score below 23.5 [41]. Both will be calculated over the first year of follow-up, as a measure for short-term disease progression (hence with direct clinical relevance for near-term treatment decisions), and over 2 years of follow-up, as a measure for mid-term prognosis.

The association between a potential biomarker and the change in the PD outcome (objective 1) will be evaluated with a multivariable linear model, adjusted for age and disease duration. For objective 2, a variety of different model building methods (e.g., forward stepwise logistic regression or lasso penalized regression methods) will be considered in the training set such that up to three candidate models may be assessed in the second half of the sample [42]. The training and testing set will be randomly selected from the entire sample. One of these models will be designated as primary for the formal assessment of objective 2 before the outcomes in the test set are unblinded. If the number of events using the split sample approach is insufficient to develop a strong model in the first half sample, cross-validation on the full sample will be considered as an alternative. For instance, as a rule of thumb, there should be no more than 1 predictor variable for every 10 events. Thus, before the data are analyzed, the list of variables to be considered may need to be trimmed.

If the selected predictors are available in the Parkinson Progression Markers Initiative (PPMI) dataset [5], this dataset will be used for external model validation. If this is not possible, at least internal validation will be performed using the test set and, if the model is refit on the full data, bootstrapping.

Additional examples of a priori hypotheses that we aim to address are, e.g.,:Activity levels extracted from the Verily Study Watch in the weeks preceding a clinic visit can predict Total and Part III scores on the MDS-UPDRS.Persons with higher levels of disease burden (including motor, affective, and cognitive symptoms) will show decreased heart rate variability when compared to persons with lower levels of disease burden.Neurocognitive testing scores predict the development of mild cognitive impairment [43, 44].Clinical motor progression in PD is the net outcome of the shifting balance between parietal hyperactivity (compensation) and basal ganglia hypoactivity (primary pathophysiology).

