### Study population

Participants are eligible for this study if they meet the following criteria:Parkinson’s disease duration ≤5 years, defined as time since the diagnosis made by a neurologist;18 years of age or older;Able to read and understand Dutch;Willing, competent, and able to comply with all aspects of the protocol, including follow-up schedules and biospecimen collections; andProviding written informed consent.

Patients with co-morbidity are explicitly NOT excluded from participation. Candidates will only be excluded in the case of existing co-morbidities that are sufficiently severe so as to hamper the interpretation of parkinsonian disability. Other exclusion criteria include contraindications to magnetic resonance imaging (MRI), pregnancy or breastfeeding, and/or nickel allergy (as components of the Study Watch contain this metal). For the lumbar puncture additional contraindications are defined, i.e., being treated with an anticoagulant medication or clinical evidence of structural cerebral abnormalities.

To guarantee a balanced study cohort, a stratification inclusion model will be applied, by gender (men/women), age (21–45;46–55; 56–65; ≥66 years) and disease duration (< 2½ years; ≥2½ years). Consequently, half of the cohort will have a disease duration of maximally 2½ years at the moment of inclusion, which will also allow us to the impact of very early signals and markers on disease progression.

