### Study procedures and assessments

Participants visit the study site three times for data collection: an initial baseline visit and two annual follow-up visits. Data collection during each visit takes a full day and can be spread out over a 1.5-day period if desired by the patient. Prior to each visit, study participants will be offered a complimentary hotel stay, thereby reducing the need for patients living far away from the study center to travel long distances in the early morning. Patients arrive at the study site in the morning in a practically defined OFF state, i.e., at least 12 h after having taken their last dopaminergic PD medication.

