		- Standing leg test	X	X	X	
		- Rapid turning test	X	X	X	
		- Pegboard test	X	X	X	
	Motor functioning in ON^a^state	- MDS-UPDRS-III (including H&Y stage)	X	X	X	
		- TUG	X	X	X	
		- MDS-UPDRS-IV	X	X	X	
		- Standing leg Test	X	X	X	
		- Rapid Turning Test	X	X	X	
		- Pegboard Test	X	X	X	
		- Grip strength	X	X	X	
	Neuropsychological symptoms	- MDS-UPDRS-I	X	X	X	
		- MoCa (with alternative versions during follow-up)	X	X	X	
		- Phonemic and semantic Fluency	X	X	X	
		- Brixton Spatial Anticipation Test	X	X	X	
		- 15 Words Test	X	X	X	
		- Benton Judgment of Line Orientation	X	X	X	
		- Letter Number Sequencing	X	X	X	
		- Symbol Digit Modalities Test	X	X	X	
	Activities of daily living	- Modified Schwab and England scale	X	X	X	
	Demographics and lifestyle	- Medical history	X	–	–	
		- Lifestyle exposure	X	–	–	
		- Medication (Parkinson and other)	X	X	X	
		- Non-pharmacologic Treatments	X	X	X	
	Biospecimens	- Stool	X	X	X	
		- EDTA Plasma (DNA)	X	–	–	
		- PAX Gene (RNA)	X	X	X	
		- peripheral blood mononuclear cells (PBMCs)	X	–	–	
		- Plasma (no PBMC)	X	X	X	
		- Serum	X	X	X	
		- CSF	X	–	X	
	Autonomic function	- Holter ECG	X	X	X	
		- 12-lead ECG	X	X	X	
		- Blood pressure (standing and supine)	X	X	X	
	Brain structure and function	- Structural MRI (T1, T2, FLAIR, DTI, QSM)	X	–	X	
		- Functional MRI (resting state, task-related)	X	–	X	
Verily Study Watch	Physiological and environmental parameters	- PPG	Continuous data collection, up to 23 h a day.			
		- ECG				
		- IMU including 3-axis accelerometer and 3-axis gyroscope				
		- EDA				
		- Skin temperature				
		- Relative humidity				
		- Barometric pressure				
		- Ambient light level				
Self reported patient questionnaires	Neuropsychological symptoms	- BDI-II				X
		- QUIP-RS				X
		- Apathy scale				X
		- STAI				X
	Sleep disorders	- SCOPA- sleep				X
		- Epworth sleepiness scale				X
	Quality of life	- PDQ-39				X
		- SF-12				X
	Various	- MDS-UPDRS-II				X
		- SCOPA- aut				X
		- RBD questionnaire				X
		- Wearing-off questionnaire				X
		- New Freezing of Gait Questionnaire				X
		- Radboud Oral Motor Inventory				X
		- Screening Questionnaire on Visual Impairment				X
		- PASE				X
Self reported caregiver questionnaires	Burden	- CSI				X

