#### Sample size considerations

For the first objective, we will test the association between potential biomarkers and the deterioration of PD on each of the two outcome domains. In this test, both the dependent and independent variables are continuous measures. In order to adjust for multiple testing issues (up to 55 biomarkers and two outcome measures) we will use a two-sided significance level of 0.05/(2 × 55), i.e., 0.00045 instead of 0.05. In order to detect an association with a correlation coefficient of at least 0.2 with a power of 90%, 565 patients are needed. Taking into account an attrition rate of 10% and missing data for approximately 3% of patients, we aim to include 650 patients in total. If additional novel biomarkers are selected for model consideration prior to the initiation of analysis, power of 80% will be retained with 100 or fewer biomarkers considered.

For the second objective we will use the dichotomous outcomes to estimate the required sample size. We will use a split sample approach to develop the model in the first half of the dataset and test it on the second half of the data. Therefore, if there are a total of 565 patients evaluable, as dictated by the power calculation for the first objective, there will be 282 patients available to assess the accuracy of the model in the test set. It is desirable to demonstrate that the accuracy is greater than 70%, i.e., the probability that the model correctly predicts whether the patient did or did not have an event using a pre-specified threshold, is larger than 70%. We will have 80% power to demonstrate that the model is more accurate than 70% if the true accuracy is 77% or higher. If sensitivity or specificity at a single cut point is lower than desired for clinical utility, power may be improved by assessing the AUC (area under the ROC curve) rather than the accuracy at a single threshold.

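### The objective-1 association model adjusts for age and disease duration but omits gender, the third factor used to stratify inclusion

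*Protocol article*

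**What the plan says.** Under Statistical analyses, the protocol article names the objective-1 model and its adjustment set: the association "will be evaluated with a multivariable linear model, adjusted for age and disease duration". No other covariate is listed.

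Under Study population, it says that "a stratification inclusion model will be applied, by gender (men/women), age" and disease duration. So three factors shape who enters the cohort, and two of them enter the model.

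The outcome is described in two ways within Statistical analyses. The objective has "progression being expressed in terms of rate of decline in two key outcome domains of the disease". The model sentence concerns "The association between a potential biomarker and the change in the PD outcome (objective 1", and it names no interval. One-year and two-year intervals do appear ("Both will be calculated over the first year of follow-up, as a measure for short-term disease progression", and then over two years), but that paragraph is written for the prediction objective.

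The testing threshold is in Sample size considerations: "we will use a two-sided significance level of 0.05/(2 × 55), i.e., 0.00045 instead of 0.05".

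**The concern.** Nothing in a cohort balances gender across levels of a biomarker. Stratified inclusion controls how many men and women enter. It does not make a marker independent of gender. If men and women differ on a marker and also progress at different rates, a marker with no relation to progression of its own will still correlate with it, and the stated model does not remove that part.

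The plan sets a strict threshold because it tests up to 55 markers on two outcomes. A Bonferroni correction protects against chance findings, not against confounding, and with 565 patients a modest induced correlation raises the rejection rate well above the nominal level.

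The two descriptions of the outcome add a smaller problem. A rate of decline, a one-year change and a two-year change are different dependent variables, and the article does not say which one objective 1 tests.

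**Working it through.** **Inputs from the article (Sample size considerations).** Two-sided α = 0.05/110 = 0.000455, correlation to detect 0.2, power 90%, 565 evaluable, 650 enrolled, attrition 10%, missing data about 3%.

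**Step 1: the plan's own figure.** By Fisher's z, N = ((z₁₋α/₂ + z_power)/atanh(r))² + 3 + k, where k is the number of covariates. With z₁₋α/₂ = 3.506, z_power = 1.282 and atanh(0.2) = 0.2027:
- k = 0: (4.788/0.2027)² + 3 = 560.7, so 561.
- k = 2 (age, disease duration): 563.

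Both agree with the stated 565. Enrolment also agrees: 565/0.87 = 649.4 and 565/(0.90 × 0.97) = 647.2, against 650. The sample size is sound.

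**Step 2: what omitting gender can do.** If a marker has no association with change once gender is known, the correlation it shows without gender is r = r(gender, marker) × r(gender, change). The probability that it is declared significant is

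Φ(atanh(r)·√562 − 3.506) + Φ(−atanh(r)·√562 − 3.506).

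The documents give neither correlation, so both are assumptions, shown as a range:

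| r(gender, marker) | r(gender, change) | induced r | false-positive rate | multiple of 0.045% |
|---|---|---|---|---|
| 0.1 | 0.1 | 0.010 | 0.06% | 1.4 |
| 0.2 | 0.2 | 0.040 | 0.53% | 12 |
| 0.3 | 0.15 | 0.045 | 0.74% | 16 |
| 0.5 | 0.2 | 0.100 | 13% | 285 |

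Using √560, to allow for age and disease duration, changes these figures only slightly (13.0% becomes 12.9%).

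**Step 3: cost of adding gender.** With k = 3, N = 564 and power at 565 is 90.1%, against 90.2% with k = 2. The power refers to a correlation of 0.2 that remains after adjustment.

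**Step 4: rate or change.** The article states that "Participants visit the study site three times for data collection: an initial baseline visit and two annual follow-up visits". With visits at 0, 1 and 2 years, the least-squares slope has weights (−0.5, 0, +0.5), so in a patient with complete, on-time visits it equals the two-year change divided by 2. The middle visit adds information mainly for patients who have no year-2 visit.

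To size this, assume that half of the 10% attrition comes after the year-1 visit. Let v be the variance of true slopes and e the measurement-error variance. The slope variance is v + 2e/4 from the two-year change and v + 2e from the one-year change. The gain is [0.05/(v + 2e)] / [0.90/(v + e/2)]. For v from 0.05 to 0.25 and e of 0.2 or 0.3 (assumed), this is 1.7% to 3.0%.

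**Step 5: why one outcome has to be named.** The divisor of 110 covers 55 markers and two outcomes, so one interval each. If the one-year and two-year changes were both tested, there would be 55 × 2 × 2 = 220 tests. At 0.05/220, power with 565 patients is 86.9%, not 90%.

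**The case against.** **Inclusion strata need not be covariates.** Stratified inclusion is not stratified randomisation, and it puts no obligation on the model. This stands. The case for gender rests on possible confounding. The strata show only that the design treats gender as important and that it is known for everyone.

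**The size is assumed.** This also stands. The article gives no gender correlations and does not list the 55 markers. With 0.1 and 0.1 the inflation is negligible, and the 13% case needs a marker strongly related to gender.

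**The full analysis plan may add gender.** It may. But the article names the adjustment set instead of leaving it open, and the set as named lacks gender.

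A reader might go further, in four ways that the documents do not support:

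- *Leaving out the baseline score is confounding.* In an observational analysis of change it is a choice of estimand. Suppose true change is unrelated to true baseline, baseline reliability is 0.7–0.9 and the marker–baseline correlation is 0.2–0.5 (all assumed). Simulation then gives a spurious correlation of about zero without baseline adjustment and 0.03–0.16 with it. The familiar variance gain of (1+ρ)/2 assumes a covariate independent of the marker, which cannot be taken for granted here.
- *The year-1 data are thrown away.* Step 4 shows that little is lost with complete visits, and the article uses one-year outcomes for prediction.
- *Patients seen only to year 1 are dropped, and the ±60-day visit window is ignored.* The article says neither, and such handling is commonly left to the full plan.
- *Baseline dopaminergic treatment must be in the model.* Medication is recorded at every visit, but the motor outcome is scored in the OFF state and treatment is itself likely to track severity. Adjusting for it is a modelling preference.

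**Conclusion.** The stated adjustment set is incomplete in one respect: it omits gender, which the design itself treats as important and which is known for every participant. Whether this produces false findings depends on how strongly gender relates to each marker and to progression, and the documents give neither. The plausible effect runs from nothing of note to a false-positive rate far above 0.045% for markers that differ strongly by gender. Because the correction is nearly free, it is worth making whichever end of the range applies.

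The mismatch between a rate of decline and an unspecified change is real but secondary. It is a matter of fixing one dependent variable, with an efficiency gain of only about 2–3% under the assumptions above. The sample size is not in question, and the documents do not support calling the unadjusted baseline score an error.

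**What to change.** 1. Add gender to the objective-1 adjustment set, alongside age and disease duration. This costs one degree of freedom and needs no new data or patients.
2. State one outcome for objective 1 and use the same term in the objective and in the model sentence. One option is a slope from a linear mixed model on all available visits with actual visit dates, testing the marker-by-time term, with gender, age and disease duration adjusted for on both intercept and slope. The other is a change over one named interval. If two intervals are to be tested, count them in the multiplicity correction.
3. Keep adjustment for the baseline MDS-UPDRS part III (OFF) or MoCA score as a sensitivity analysis, and say that it estimates change conditional on the starting score. Adjustment for baseline dopaminergic treatment can be left to the analysts' judgement, with a reason given.

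The cost is plan wording and a few lines of model code.

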#### Sample size considerations

For the first objective, we will test the association between potential biomarkers and the deterioration of PD on each of the two outcome domains. In this test, both the dependent and independent variables are continuous measures. In order to adjust for multiple testing issues (up to 55 biomarkers and two outcome measures) we will use a two-sided significance level of 0.05/(2 × 55), i.e., 0.00045 instead of 0.05. In order to detect an association with a correlation coefficient of at least 0.2 with a power of 90%, 565 patients are needed. Taking into account an attrition rate of 10% and missing data for approximately 3% of patients, we aim to include 650 patients in total. If additional novel biomarkers are selected for model consideration prior to the initiation of analysis, power of 80% will be retained with 100 or fewer biomarkers considered.

For the second objective we will use the dichotomous outcomes to estimate the required sample size. We will use a split sample approach to develop the model in the first half of the dataset and test it on the second half of the data. Therefore, if there are a total of 565 patients evaluable, as dictated by the power calculation for the first objective, there will be 282 patients available to assess the accuracy of the model in the test set. It is desirable to demonstrate that the accuracy is greater than 70%, i.e., the probability that the model correctly predicts whether the patient did or did not have an event using a pre-specified threshold, is larger than 70%. We will have 80% power to demonstrate that the model is more accurate than 70% if the true accuracy is 77% or higher. If sensitivity or specificity at a single cut point is lower than desired for clinical utility, power may be improved by assessing the AUC (area under the ROC curve) rather than the accuracy at a single threshold.

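### Objective 1 uses a single-step Bonferroni cut-off for up to 110 tests; the cut-off is valid, but Holm's procedure gives the same error control and never rejects less

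*Protocol article*

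**What the plan says.** Under Statistical analyses, objective 1 concerns "The individual associations between potential biomarkers and disease progression in Parkinson’s disease", with progression measured on two outcomes, MDS-UPDRS part III in the OFF state and MoCA. Each association "will be evaluated with a multivariable linear model, adjusted for age and disease duration". That section names no multiplicity procedure.

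The multiplicity rule stands under Sample size considerations: "In order to adjust for multiple testing issues (up to 55 biomarkers and two outcome measures) we will use a two-sided significance level". The figure is given as a "two-sided significance level of 0.05/(2 × 55), i.e., 0.00045 instead of 0.05". The sample size follows from it: "In order to detect an association with a correlation coefficient of at least 0.2 with a power of 90%, 565 patients are needed". Enrolment is then raised to 650 for 10% attrition and about 3% missing data. If further biomarkers are added, the article states that "power of 80% will be retained with 100 or fewer biomarkers considered".

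**The concern.** The sentence on the significance level says what will be done, and no other rule for objective 1 appears. Read plainly, the figure is therefore the decision rule as well as the basis for the sample size. Every p-value is compared with 0.05/110, however many other associations have already been declared.

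Holm's procedure compares the smallest p-value with 0.05/110, the next with 0.05/109, and so on until one fails. It needs no assumption about dependence. Used only to decide which associations to declare, single-step Bonferroni gives no better guarantee in return for its lower power. What is at stake is a few real associations with p-values just above 0.05/110, which Holm would declare and the fixed cut-off would not. False discovery rate control would replace the plan's error criterion; Holm keeps it.

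**Working it through.** **Inputs from the article (Sample size considerations).** Two-sided family-wise level 0.05; up to 55 × 2 = 110 tests; correlation 0.2; power 90%; 565 evaluable and 650 enrolled.

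**1. The plan's own figures.**
- Per-test level: 0.05/110 = 0.000455 (printed as 0.00045); two-sided critical z = 3.506.
- Fisher z sample size: n = ((z_crit + z_power)/atanh(r))² + 3 = ((3.506 + 1.282)/0.2027)² + 3 ≈ 561. The article's 565 is within 1% of this.
- Power at 565: Φ(√562 × 0.2027 − 3.506) = Φ(4.806 − 3.506) = Φ(1.300) = 90.3%.
- Enrolment: 565/(1 − 0.13) = 649.4, hence 650.
- With 100 biomarkers (200 tests, level 0.05/200), power is 87.4%, so the article's 80% statement is safe.

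The plan therefore reproduces and has its planned power.

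**2. Holm at the same n and r = 0.2.** After k rejections the level is 0.05/(110 − k).

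| Earlier rejections k | Level | Power at n = 565 |
|---|---|---|
| 0 | 0.000455 | 90.3% |
| 5 | 0.000476 | 90.5% |
| 10 | 0.000500 | 90.7% |
| 20 | 0.000556 | 91.2% |

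The first step is identical to Bonferroni. The gain comes only after other associations have been declared.

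**3. Holm over the whole family.** Simulation of 110 independent z statistics at n = 565 (independence, the number of true associations and their size are assumed; 40,000 replicates):

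| True associations | r | Bonferroni power | Holm power | Studies with at least one extra rejection |
|---|---|---|---|---|
| 5 | 0.20 | 90.3% | 90.5% | 0.9% |
| 5 | 0.15 | 53.1% | 53.3% | 1.2% |
| 20 | 0.20 | 90.3% | 91.0% | 15% |
| 20 | 0.15 | 53.1% | 54.2% | 19% |

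Holm's simulated family-wise error stayed below 5% in all four cases. The value r = 0.15 lies below the effect that the study was sized for and is shown only for range.

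**4. Resampling (single-step max-T), as an option.** Its gain depends on the correlation among biomarkers, which the documents do not give. All values below are assumed; n = 565.

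| Assumed correlation among the 55 biomarkers | Power at r = 0.20 | Bonferroni's actual family-wise error |
|---|---|---|
| Equal, 0 to 0.3 | 90-91% | 4.0-5.1% |
| Equal, 0.5 | 92% | 3.3% |
| Equal, 0.7 | 94% | 2.1% |
| Six modality blocks, 0.5-0.8 within and 0.1 between | 91-93% | 2.9-4.4% |

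Against 90.3%, that is about 0-1 point for correlations up to 0.3, and about 1-3 points under modality blocks.

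**The case against.** The strongest reply is that nothing needs mending. The cut-off is valid, the sample size reproduces and the planned power is met. That stands, and it is why the point is an improvement and not an error.

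A second reply is that the level appears only under the sample size heading, and that a condensed article may leave the choice between single-step and step-down testing to an analysis plan that is not shown. This has some force. But the article does not leave the matter open: it states the level to be used and offers no other rule. If the analysis plan already specifies Holm, the point falls away.

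Third, a fixed cut-off has practical merits. It is known in advance, does not depend on the other tests, and leads directly to simultaneous confidence intervals. These merits are real, but they concern reporting, not which associations are declared. Bonferroni-adjusted intervals can still be reported beside Holm decisions.

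A reader might infer more: that Bonferroni here runs far below 5%, and that resampling would lift power to 93-96%. That needs all 55 biomarkers to be equally correlated at 0.6 to 0.8. The article gives no correlations, and Table 1 draws on stool, blood, CSF, MRI, ECG and watch sensors, for which such uniform correlation is not supported. Permutation of model residuals is also approximate and must cope with unequal missing data, since CSF is optional.

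A reader might also infer a further loss from testing both the 1-year and the 2-year change. For objective 1 the article counts two outcome measures only, and its list of objectives attaches the two time points to prediction, which is objective 2.

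**Conclusion.** The point holds as a free improvement of low severity. It shows no error, no contradiction and no shortfall in power. That Holm is never worse than the stated rule requires no assumption about the data. Its size does: under independent tests the gain is about 0.2 point of power per true association with 5 true associations and about 1 point with 20. It is nil for a study with a single detectable association, because Holm's first step is Bonferroni. The larger gains from resampling remain conditional on correlations that the documents do not provide.

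**What to change.** Keep 0.05/110 as the basis for the sample size. Add one sentence to the analysis section, before outcome data are analysed: the objective 1 p-values from all biomarker-by-outcome tests will be judged together by Holm's step-down procedure at a two-sided family-wise level of 5%, with the number of tests set to the final biomarker list times two outcomes.

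The cost is that sentence. The targets of 565 evaluable and 650 enrolled patients stay as they are, no new data are needed, and the thresholds are still known in advance given the ordering of the p-values.

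Step-down max-T permutation may be considered instead. It would then have to be specified in advance, including how it treats covariates and biomarkers with different numbers of patients, such as CSF markers.
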